### Intervention

#### Manuals

The CBT manual [8] is well established. The goal is to establish a realistic self-perception. It includes: 1) generation of an idiosyncratic version of the disorder and identification of individual safety behaviors; 2) manipulation of self-focused attention and safety behaviors in role plays, and using video feedback to demonstrate their adverse effects; 3) training in attentional redeployment and reduction of safety behaviors through behavioral experiments (expositions), cognitive restructuring and changing of dysfunctional convictions; 4) relapse prevention; 5) booster sessions after the end of therapy to refresh therapeutic gains.

The ST manual was written by JS and CH, with consultations from [name] (Heidelberg University Hospital). It is the first manual that reviewed ST manuals for social anxiety disorders in child and adolescent psychotherapy [19] and well-established ST manuals for different disorders [20–22], in addition to the well-written CBT and PD manuals for social anxiety disorders [8, 56, 57]. It is based on general ST concepts [18], integrating constructivist, solution-oriented [5, 23] and strategic [24–27] methods, in addition to attending disorder-specific relational ST dynamics [19, 28, 29]. JS and CH tested the manual with two patients before teaching it to the study therapists. Training experiences were utilized for a last revision before study therapies started. According to this manual [30], ST combines three different therapy settings with different participants in a multisystemic therapy concept. The first two therapies, and the majority of all therapy sessions alike, are individual but with a strong focus on relationship issues. They are combined with sessions with partners, parents or closest friends, and with one 3-hour group therapy session bringing together project patients and therapists. The ST manual differentiates between four phases: 1) generation of an idiosyncratic version of the function of the social anxiety symptoms including the identification and inclusion of important private and/or professional social systems and the important members within these systems; 2) experimentation with changes through symptom prescription, paradoxical intention, externalization, deconstruction of shared belief systems and enactment of socially anxious interactions with and without important social system members; 3) relapse prevention involving important social system members; and 4) booster sessions after the end of therapy including important social system members to gain a shared refreshment of therapeutic gains.

#### Training and supervision

All therapists participated in a 3-day CBT or ST training. [name] (Institute of Psychology, Johann Wolfgang Goethe University of Frankfurt, Germany) conducted the CBT workshops; JS and CH conducted the ST workshops. Supervisions were obligatory for one out of four therapy hours. [name] and [name] (CPP) supervised the CBT group; JS supervised the ST group.

#### Adherence

Therapists will estimate their adherence after each session. Independent raters will rate therapy session video recordings for manual adherence. We are currently developing a Systemic Therapy Adherence Scale (STAS) and will utilize the Cognitive Therapy Adherence Scale for Social Phobia (CTACS) [58] as well.

### Participation and attrition, responses to crises and suicidality

We will measure participation and attrition by counting the number of interested persons who will 1) contact the recruiting office, 2) participate in the initial screening, 3) will be SCID-interviewed, 4) included into the pilot study, 5) drop out before the beginning of therapy, 6) start therapy, 7) drop out during therapy, 8) end therapy, 9) participate in the 9 months follow-up, and 10) participate in the 12 months follow-up. We will describe causes for withdrawing, and calculate the retention rate for both study conditions separately and together.

Patients will be instructed to contact the therapist and/or research team whenever experiencing adverse events. No constraints will exist regarding additional therapeutic consultations. Inclusion criteria will, however, not allow for use of additional counseling or therapeutic support during the study period.

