### Psychotherapy

CBT explains the disposition of social anxiety disorders by cognitive schemas which stimulate misleading internal information processing. Socially anxious individuals show increased self-focused attention when interacting with others stimulated by the assumption that others can see their anxiety. Based on a linked reduction in observation of other people, they focus on negative reactions and tend to interpret ambiguous and neutral feedback in a negative way. This results in excessively negative inferences about how they appear to others. Incorrect cognitions induce avoidance of social situations and/or the extensive use of safety behavior (e.g. avoiding eye contact, speaking low). The intention is on the prevention of feared catastrophes. However, avoidance and safety behavior contributes to the maintenance of negative beliefs and the increase of feared symptoms. They make patients come across to others in ways that are likely to elicit less friendly responses [8, 16, 17].

CBT aims to reverse the maintaining processes specified in the cognitive model of Clark and Wells [17]. The goal is to establish a realistic self-perception. The CBT manual [8] differentiates between five phases which are described in detail in the method section.

ST explains the development of social anxiety disorders by reciprocal interpersonal interactions. Symptoms of social anxiety serve the near-distance regulation when interacting with others. They represent the (non-verbal) communication of dyadic or multi-person “between-us” quality of relationship in private (e.g. family, couple, friends) or professional (e.g. work colleagues, superior-inferior) social systems. Social anxiety indicates that an actual development task has not yet been accomplished and that socially anxious behavior, feelings and thoughts appear to be the best solution currently available. ST thus interprets social anxiety as an individual’s sensitive reaction when fearing being scrutinized and socially rejected. However, maintaining social system structures reciprocally maintains social anxiety [18, 19].

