### Recruitment

#### Patients

Recruitment started in 2014, with the first patient included on 18 November 2014, and we expect to complete recruitment in spring 2016. We distributed flyers and study information to doctors, psychological psychotherapists, occupational therapists, hospitals and psychosocial counseling centers in and around Heidelberg; gave public announcements in the local press, on the IMP website, information portals on clinical trials and Facebook; mailed to the Heidelberg University, the Heidelberg University Hospital and universities near Heidelberg; and we gave our flyer and study information to the outpatient centers of the CPP, IMP and the Central Institute of Mental Health in Mannheim. All patients will present themselves to the study team and no patients will be referred.

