##### Follow-up (T6 and T7)

We will assess patients at 9 and 12 months after the beginning of therapy. Again, patients will participate in the online survey including the outcomes (Table 1). The assessment will be conducted at the IMP. The study will close 12 months after the beginning of therapy of the last included patient.

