#### Clustering effects

CBT and ST will be administered in two independent centers. There will be considerable interaction among the therapists within each study arm, particularly during training and supervision. Within the ST condition, there will also be interaction between patients, above all in the group therapy session. Due to data dependency, we will conduct two-level (patients, treatment condition) linear regression analysis to account for positive intra-class correlations (ICCs) with respect to the primary outcome measures [91, 92].

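### The only adverse-event method the article states is patient-initiated contact, and Table 1 has no adverse-event row, so events may be missed, most of all after therapy ends

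*Protocol article*

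**What the plan says.** The section on participation, attrition and crises states the method: "Patients will be instructed to contact the therapist and/or research team whenever experiencing adverse events". It adds that "No constraints will exist regarding additional therapeutic consultations", and then recalls that the inclusion criteria rule out further counseling or therapy during the study. It describes no scheduled enquiry about adverse events.

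Table 1 sets out the instruments from screening to T7. It covers social anxiety, diagnoses, functioning, depression, general symptoms, relationships, caregiver burden, process measures, therapist factors, adherence and service use. No row concerns adverse events, negative effects of therapy or crises. The sections on therapy and follow-up describe an online survey that includes the Table 1 outcomes.

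On follow-up: "We will assess patients at 9 and 12 months after the beginning of therapy". Regular therapy ends at T5, and both manuals provide only booster sessions after that. On the systemic therapy (ST) manual, the Manuals section says that its authors "tested the manual with two patients before teaching it to the study therapists".

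**The concern.** A method that waits for the patient to speak up records only what patients choose to raise. The article's account of the disorder gives some reason for caution: "Incorrect cognitions induce avoidance of social situations and/or the extensive use of safety behavior". After T5 the regular contact with a therapist, in which a problem might come up unprompted, is gone, although observation continues to 12 months.

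What is at stake is the harm record of this pilot, not its effect-size work. The ST manual is new for this disorder and had been tried with two patients before the study therapists were taught it. The pilot is meant to inform a confirmatory trial, so its adverse-event count will be early evidence on the manual. Under passive report, a low or zero count could mean few harms or few reports.

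**Working it through.** **1. Text against schedule.** The crisis section names one route, contact by the patient. Table 1 has no adverse-event row at any of T1 to T7. The planned sources that could show harm indirectly are:

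- LSAS-SR, SIAS, SPS, BDI-II and BSI at T1 to T7: symptom worsening, but not events as such.
- SCID and GAF at T5: a diagnostic picture at the end of therapy, with neither repeated at T6 or T7.
- CSSRI-EU at T5 to T7: service use, described for costing.
- Reference-person ratings (BSI, ASS and the burden scale among them) up to T7: a second informant on symptoms and burden.
- Causes of withdrawal: only for patients who leave.

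None of these is described as asking about adverse events.

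**2. What a zero count would mean.** The article states no adverse-event figure, so there is nothing to reproduce. Inputs: 16 patients per arm and 32 in total (Design and sample size). The capture rate s, meaning the share of affected patients who report, is my assumption. With no recorded event among n patients, the one-sided 95 % upper limit for the recorded rate is 1 − 0.05^(1/n). Dividing by s gives the limit for the true rate.

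| n | s = 1 | s = 0.75 | s = 0.5 |
|---|---|---|---|
| 16 | 0.171 | 0.228 | 0.341 |
| 32 | 0.089 | 0.119 | 0.179 |

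**3. Chance of recording anything.** With an assumed true rate of 10 % in an arm of 16, the chance of recording at least one affected patient is 1 − (1 − 0.10 × s)^16. This is 0.815 for s = 1, 0.560 for s = 0.5 and 0.333 for s = 0.25.

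**4. Surveys still usable.** From the start there are 32 × 6 = 192 surveys at T2 to T7, of which 32 × 2 = 64 are T6 and T7. The recruitment section reports the trial "with the first patient included on 18 November 2014, and we expect to complete recruitment in spring 2016", and the article appeared on 31 March 2016, 499 days after that first inclusion. I assume even accrual of 32 patients and no attrition.

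- Recruitment ends 31 March 2016, therapy starts at inclusion. T6 past: 32 × (499 − 274)/499 = 14.4. T7 past: 32 × (499 − 365)/499 = 8.6. Left: 64 − 23.0 = 41.0.
- Recruitment ends 20 June 2016 (accrual over 580 days), therapy starts two months (61 days) after inclusion. T6 past: 32 × (499 − 61 − 274)/580 = 9.1. T7 past: 32 × (499 − 61 − 365)/580 = 4.0. Left: 50.9.

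So about 41 to 51 of the 64 T6 and T7 surveys were still ahead at publication. The remaining T2 to T5 surveys cannot be counted, because they are timed by therapy hour or by the end of therapy.

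**The case against.** The strongest reply is that this is a condensed article, and that the sentence reads as a safety instruction to patients, with the recording procedure left to the full protocol. That limits the wording to what the article states. It does not remove the point, because the article names a method and prints the schedule beside it.

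Several further replies stand:

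- The survey is described as including the Table 1 outcomes, which need not be its whole content. A reader might infer that the surveys contain no adverse-event item. The text supports only that Table 1 has no such row.
- A reader might infer that socially anxious patients will probably under-report. The avoidance passage comes from the cognitive model of the disorder and is not evidence about telling one's own therapist of a problem. Every patient approached the study team without referral, sees a therapist for up to 26 hours and is assessed at the institute, including at T6 and T7. Therapies are recorded, and "Supervisions were obligatory for one out of four therapy hours". Events may be missed, but the documents do not establish that many will be.
- The scheduled scales and the reference person would reveal some deterioration.
- Even with full capture, 16 patients per arm leave an upper limit of 17 %, so the pilot is imprecise on harms either way.

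A reader might also infer a bias between the arms, since "CBT and ST will be administered in two independent centers" and therapists differ by arm. The research-team route is open to both arms, no comparison of adverse events is planned, and neither size nor direction can be derived. The documents do not support that claim.

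**Conclusion.** The point holds as a minor one. The only stated adverse-event method is passive, the printed schedule adds no adverse-event row, and events may be missed, chiefly between T5 and T7. The size is not derivable. The limits of 17, 23 and 34 % for an arm, and 9, 12 and 18 % for the whole trial, rest on assumed capture of 100, 75 and 50 %. They describe how much weaker a zero count becomes and say nothing about a difference between arms. Planned effect sizes, the sample size for the main trial and the efficacy analyses are unaffected. If the full protocol contains a scheduled enquiry, the point falls away.

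**What to change.** Keep patient-initiated contact for urgent help. Add one or two fixed adverse-event and crisis questions, worded identically in both arms, to the existing online survey at the remaining T2 to T7 visits.

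Clinical follow-up of positive answers can go to the existing supervisors. Events should be counted from the patients' answers by one rule for both arms and not by supervisor judgment, because supervisors differ by arm and the ST supervisor co-wrote the ST manual. Keep these answers away from the blinded SCID assessors.

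Report descriptively by arm, with the number assessed:

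- patients with any adverse event, with solicited and spontaneous reports shown separately;
- patients whose LSAS-SR, SIAS, SPS or BDI-II has deteriorated from T1 beyond a reliable-change threshold stated in advance. Counting any worsening would mostly count measurement noise.

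The cost is one or two items in a survey that patients already complete, plus a little follow-up work. Ascertainment will be mixed for patients already enrolled, more minor events will be recorded, and deterioration on a scale is not proof of harm from therapy. Sample size and efficacy analyses do not change.

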### Measures

#### Screening and assessments

In the screening phase, interested persons will receive pilot study information, will be asked for the fulfillment of inclusion and exclusion criteria, and will be SCID-interviewed for a social anxiety disorder. Potential patients will receive the LSAS-SR and screening questions for the SCID interview. In bi-centric case conferences, supervising experts of both the CPP and IMP, together with the SCID-diagnosticians, will discuss whether the cases will fulfil the inclusion criteria.

##### Primary outcome measures: social anxiety

The 24-item LSAS-SR assesses social interaction and performance situations feared and the degree of avoidance in the past week [59, 60] with excellent internal consistency [61] and good sensitivity to change [45]. The 20-item SIAS and SPS assess social anxiety in interpersonal interactions (SIAS) or while being observed by others (SPS) with good to excellent internal consistencies and sensitivity to change [41–43].

##### Secondary outcome measures: psychological functioning

The GAF scale measures clinicians’ evaluation of patients’ psychosocial functioning [62, 63] with high levels of interrater reliability [64] and sensitivity to change [62]. The 21-item Beck Depression Inventory II (BDI-II) detects cognitive, motivational, affective and somatic symptoms of depression with excellent to good internal consistencies [65, 66] and high sensitivity to change [67]. The Brief Symptom Inventory (BSI) assesses a variety of mental symptoms, and is highly correlated to the original SCL-90-R [68–70].

##### Social system and interpersonal functioning

The 12-item Experience in Social Systems Questionnaire (EXIS) assesses patients' experience within their important social systems. The EXIS shows excellent to satisfactory internal consistencies and good sensitivity to change [71]. The 12-item Dyadic Adjustment Scale (DAS-12) measures the quality of marital relationships showing satisfactory internal consistency [72]. We apply the DAS-12 not only to romantic or marital partners, but also to other caregivers (e.g. family member, best friend). The 32-item Inventory of Interpersonal Problems (IIP-32) identifies a person’s interpersonal difficulties revealing excellent to satisfactory internal consistencies [36, 73] and satisfactory sensitivity to change [74].

##### Symptom adjustment

We developed a 5-item Adjustment to Symptomatology Scale (ASS), inspired by the Couples Interaction Checklist (CIC) [75], but with a focus on a patient’s adjustment to psychological problems in terms of social interactions between the patient and significant others. We are currently investigating its psychometric structure in a separate research project [76].

##### Caregiver burden

The 19-item Burden Assessment Scale (BAS) measures burden by intimate others with excellent to good internal consistencies and satisfactory sensitivity to change [77]. Our German validation found the BAS psychometric reliable with good internal consistencies [78].

##### Change measures

The 21-item Scale for the Multiperspective Assessment of General Change Mechanisms in Psychotherapy (SACiP) measures general change mechanisms with excellent to satisfactory internal consistencies and demonstrated validity by predicting outcome [79, 80]. The 4-item Session Rating Scale (SRS) measures therapeutic alliance [81], and its validity is confirmed by positive correlations with outcome [82]. The 16-item University of Rhode Island Change Assessment Scale (URICA) measures stages of change with excellent to satisfactory internal consistencies and demonstrated validity by predicting symptoms [83].

##### Credibility

The Opinion About Treatment (OAT) questionnaire, adapted from Borkovec and Nau’s (1972) credibility and expectancy questionnaire, assesses how successfully patients think the treatment will be and appears with excellent internal consistencies [84]. We will adapt the OAT to a therapist version as well.

##### Therapist variables

The Development of Psychotherapist Common Core Questionnaire (DPCCQ) characterizes therapists on several subscales [85], of which we chose interpersonal style, relational skills, quality of therapists’ personal lives and difficulties in practice to be suitable for this pilot study. The scales have been found predictive of the therapeutic alliance and outcome [86–88].

##### Service receipt

The Client Sociodemographic and Service Receipt Inventory (CSSRI-EU) can be used for the calculation of costs for health service utilization and medication [89]. Face validity and cross-cultural adaptation are achieved [90].

### Statistical analyses

All statistics will be descriptive and explorative using the SPSS statistical package (version 19.0; IBM, Frankfurt, Germany). In addition to descriptive measures such as mean, standard deviation, median, interquartile range and confidence intervals, comparisons of primary endpoints between the two groups will be performed using t-test, Mann–Whitney U test and chi-square test, as appropriate. Missing values on less than 20 % of items for each scale of all outcome measures will be replaced with the conditional mean values for the CBT or ST group.

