##### Therapy (T1 to T5)

We will assess study outcomes before the start of therapy, after the 8th, 15th and 20th hour of therapy, as well as after therapy has ended. At each time of assessment, patients will participate in an online survey (UNIPARK) including study outcomes (Table 1). The assessment will be conducted at the IMP. Baseline data (T1) will be scheduled no more than 5 days before the first therapy session. Therapy process (T2 to T4) will be assessed no more than 5 days after the 8th, 15th and 20th hour of therapy. The primary endpoint (T5) will be defined by a joint patient-therapist decision to end therapy or by the end of 26 hours of therapy. All outcome variables will be assessed anew, along with in- and outpatient health care service data. A post-SCID and social network interview will also be conducted. Like the pre-SCID, the post-SCID interviews will be rated by independent raters considering primary and secondary diagnoses.

**Table 1 Tab1:** Assessment measures and application plan

Purpose	Perspective	Domain	Instrument	Screening	Baseline	8th, 15th, 20th hour of therapy	End of therapy, no later than 26th hour of therapy	9 and 12 months after beginning of therapy
					T1	T2 to T4	T5	T6 and T7
Screening	Pat	Social anxiety	LSAS-SR	X				
	Diag	Mental disorder SAD	SCID: SAD	X				
Outcome	Diag	Mental disorders	SCID I, II	X			X	
	Pat	Social anxiety	LSAS-SR	X	X	X	X	X
	Pat	Social anxiety	SIAS	X	X	X	X	X
	Pat	Social anxiety	SPS	X	X	X	X	X
	Diag	Global functioning	GAF	X	X		X	
	Pat	Depression	BDI-II	X	X	X	X	X
	Pat, Ref	General symptom severity	BSI	X	X	X	X	X
	Pat, Ref	Experience of social systems	EXIS	X	X	X	X	X
	Pat, Ref	Evaluation of social systems	EVOS	X	X	X	X	X
	Pat, Ref	Dyadic adjustment	DAS-12	X	X	X	X	X
	Pat	Interpersonal problems	IIP-32	X	X	X	X	X
	Pat, Ref	Symptom adjustment	ASS	X	X	X	X	X
	Ref	Burden	BAS		X	X	X	X
Process	Pat, T	Therapeutic alliance	SACiP			X	X	X
	Pat, T	Therapeutic relationship	SRS			X	X	X
	Pat	Therapy motivation	URICA			X	X	X
	Pat, T	Credibility	OAT		X			
Therapists	T	Common therapist factors	DPCCQ		X	X	X	X
Quality	R	Adherence and competence	STAS, CTAS-SP		X	X	X	X
Additional service	Pat	Service receipt	CSSRI-EU				X	X

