#### Mixed-design ANOVA

We will perform mixed-design ANOVA to identify differences between treatment conditions [95]. Factors will be group (CBT or ST) and time (baseline, 8th, 15th, 20th therapy hour, end of therapy, respectively 26th therapy hour, 9 and 12 months after the beginning of therapy). Contrasts A will compare baseline with end of therapy. Contrasts B will indicate change between end of therapy, respectively 26th therapy hour, and 9 months after the beginning of therapy. Contrasts C will indicate change between end of therapy and 12 months after the beginning of therapy. We will control for differences in the length of treatment.

Time X Group interaction effect sizes will be assessed with partial eta-squared (η^2^) for the mixed-design ANOVA. Classification of effect sizes will be: η^2^ ≥ 0.01, small effect; η^2^ ≥ 0.06, medium effect; and η^2^ ≥ 0.14, large effect. Subsequently, for significant Time X Group interactions, simple effect analyses within and between groups will be performed [96]. Between-group effect sizes will be assessed with η^2^ and Cohen’s *d*. Classification of Cohen’s *d* will be: *d* ≥0.20, small effect; *d* ≥0.50, medium effect; and *d* ≥0.80, large effect [34]. In accordance with Coe [97], we will interpret Cohen’s *d* in terms of percentiles. Within-group effect sizes will be assessed with η^2^.

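### Neither planned between-group analysis of the primary outcomes adjusts for baseline as a covariate, and the protocol does not say which one supplies the effect size for the main trial

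*Protocol article*

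**What the plan says.** Under Statistical analyses, the article plans that "comparisons of primary endpoints between the two groups will be performed using t-test", with a Mann–Whitney test or a chi-square test where those suit better. It names no covariate there and opens the section with "All statistics will be descriptive and explorative using the SPSS statistical package".

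Under Mixed-design ANOVA, a second between-group analysis is planned: "We will perform mixed-design ANOVA to identify differences between treatment conditions". Its factors are group and seven time points including baseline, and "Contrasts A will compare baseline with end of therapy". The only control named is length of treatment. Both eta-squared and Cohen's d are to be reported between groups, without saying whether d refers to end scores or to change.

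Under Clustering effects, a two-level regression on the primary outcome measures is added, again with no baseline covariate named.

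Baseline scores will exist. Table 1 marks LSAS-SR, SIAS and SPS at T1 and T5, and the text on T1 to T5 says "Baseline data (T1) will be scheduled no more than 5 days before the first therapy session". The primary endpoint is T5: "The primary endpoint (T5) will be defined by a joint patient-therapist decision to end therapy or by the end of 26 hours of therapy". The Hypotheses section makes the size of the ST-versus-CBT effect the main question, for use in sizing the next trial.

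**The concern.** The trial's main product is one number per scale: the group difference at the end of therapy. The article offers two main routes to it. One uses only the T5 scores. The other subtracts baseline in full. Both respond to a chance difference in baseline severity, in opposite directions, and with 32 patients such differences are common. Because no order is set between the routes, the planning effect size could be taken from either after the results are seen.

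Both routes also give up precision that the collected baseline scores could provide. The stake is not a failed test, since the pilot makes no confirmatory claim. It is a noisier and ambiguous input to the main trial's sample size.

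**Working it through.** **Inputs from the article.** 16 patients per arm, 1:1; worthwhile difference 0.3 SD; main trial of 350 at 80% power and two-sided 5%; pilot of 32 from a one-sided 80% confidence limit (Design and sample size). **Assumed, not in the article.** Correlation r between baseline and T5 scores, taken as 0.4 to 0.7 and shown from 0.3; equal SDs at both times; complete data.

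**1. The article's own figures.** Main trial: 2 × ((1.960 + 0.842)/0.3)² = 174.4, so 175 per arm and 350 in total. Pilot: 2 × (0.842/0.3)² = 15.7, so 16 per arm and 32 in total; 32/350 = 9.1%. Both reproduce.

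**2. How far apart the two estimates can be.** Group difference in change = T5 difference − baseline difference. The t-test estimate and Contrast A therefore differ by exactly the baseline difference (before any control for length of treatment). Its standard error under chance is √(2/16) = 0.354 SD.
- P(imbalance over 0.3 SD) = 2 × (1 − Φ(0.3/0.354)) = 0.396, about 40%.
- P(imbalance over 0.5 SD) = 2 × (1 − Φ(0.5/0.354)) = 0.157, about 16%.

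**3. How much of it reaches each estimate.** Given a baseline imbalance b, the T5 difference shifts on average by r × b, and the change contrast by −(1 − r) × b. With b = 0.3 SD and r = 0.5 the shifts are +0.15 and −0.15. If the true difference is 0.3 SD and the imbalance lies in the same direction, the two analyses read on average 0.45 and 0.15. Scaling the article's 350 gives 350 × (0.3/0.45)² ≈ 156 and 350 × (0.3/0.15)² = 1,400. Baseline adjustment removes the average shift.

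**4. Precision.** Variance of the group difference, relative to the t-test on T5 scores: t-test 1; change contrast 2(1 − r); ANCOVA (1 − r²) × (1 + 1/(32 − 4)) = (1 − r²) × 1.036, where the last factor is the small-sample cost.

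| r | Change | ANCOVA | ANCOVA saving v t-test | ANCOVA saving v better planned analysis | 95% half-width in SD: t-test / change / ANCOVA |
|---|---|---|---|---|---|
| 0.3 | 1.40 | 0.943 | 6% | 6% (t-test) | 0.72 / 0.85 / 0.70 |
| 0.4 | 1.20 | 0.870 | 13% | 13% (t-test) | 0.72 / 0.79 / 0.67 |
| 0.5 | 1.00 | 0.777 | 22% | 22% (equal) | 0.72 / 0.72 / 0.64 |
| 0.6 | 0.80 | 0.663 | 34% | 17% (change) | 0.72 / 0.65 / 0.59 |
| 0.7 | 0.60 | 0.528 | 47% | 12% (change) | 0.72 / 0.56 / 0.53 |

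Below r = 0.5 the t-test is the better planned analysis; above it the change contrast is. The saving against the better one peaks at r = 0.5: 25% in large samples, 22% with the small-sample factor.

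**5. When adjustment does not pay.** ANCOVA beats the t-test if (1 − r²) × 1.036 < 1, that is, if r exceeds about 0.19.

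**The case against.** The fairest defence has four parts.

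- The sentence on t-tests is a general menu: a chi-square test does not suit continuous scores, so it need not fix a primary model. The ANOVA section is more specific and does use baseline. This stands in part. A reader might infer that the plan ignores baseline altogether, and that would be wrong. But a change score is not covariate adjustment, and the article ranks neither analysis above the other.
- A reader might infer that a quarter or more of the information is wasted. The document does not support that. It gives no correlation; a 25% loss against the t-test needs r of at least 0.50 (0.53 with the small-sample factor); and against the better planned analysis the loss never exceeds 25%.
- A reader might also infer that a baseline imbalance passes in full into the t-test difference, or that the test is biased. Only a fraction r passes on average, and over repeated randomizations the unadjusted difference is unbiased. The problem is conditional on the imbalance that occurs.
- The trial is explorative, its size does not rest on power, and covariate lists are often left to a fuller document. This limits the consequence. It does not remove the point, because the article states the tests and also makes the effect size its main question.

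**Conclusion.** The point holds as one of efficiency and clarity, not as an invalid analysis. The article plans two analyses of the same outcome that chance baseline imbalance pushes in opposite directions, and does not say which supplies the planning effect size. The gap between them needs no assumption about r: it exceeds 0.3 SD, the article's own worthwhile difference, in about 40% of trials of this size, given complete data and no further covariate. The precision gain does depend on r: about 13% to 47% against the t-test for r of 0.4 to 0.7, and at most about 22% against the better planned analysis, with equal SDs assumed.

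Adjustment will not make the estimate precise. At r = 0.5 the 95% half-width is still 0.64 SD. The change is worth making because it costs almost nothing and settles which number is used.

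The argument does not imply that LSAS-SR should become the only primary outcome. The article lists LSAS-SR, SIAS and SPS as primary measures, and the case for adjustment applies equally to each.

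**What to change.** For each of LSAS-SR, SIAS and SPS, state that the main estimate, and the source of the planning effect size, is the T5 group difference from a linear model adjusted for that scale's baseline score, with its confidence interval. Keep the t-test, the Mann–Whitney test and the change contrast as description.

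State which baseline score is used. By the order of steps described, T1 comes after patients are told their arm, so a pre-randomization score is preferable where it is collected. The screening text names only LSAS-SR, whereas Table 1 also marks SIAS and SPS at screening; confirm whether those two are collected then, and use T1 if not. One trade-off should be noted: the screening LSAS-SR is restricted to scores above 30 and lies further from T5, so its correlation with T5 may be lower than that of T1.

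The cost is a wording change, the check on SIAS and SPS, and one degree of freedom: about 3.6% in variance at 32 patients, which outweighs the gain only if r is below about 0.2.
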